## Statistical analysis

### Baseline characteristics

All subjects who were invited to participate in this trial will be accounted for, and a CONSORT flow chart will be prepared for both the stage 1 and stage 2 participants. Reasons for early withdrawal will be listed for all participants who prematurely withdraw from the study. The number of participants who are screened but not randomised will be presented and the reasons for their non-participation will be listed (where available). The number of participants who are randomised, the number who fulfil eligibility criteria, and the number who satisfy elimination criteria at the specified time-points in the study will be summarised. The number of participants randomised by study centre and the rate of accrual over time will also be reported.

The trial participants will be summarised according to baseline variables. The data for each baseline variable will be presented descriptively. Quantitative variables will be summarised by median and inter-quartile range (IQR). Qualitative variables will be summarised by counts and proportions.

Summaries of the following listed baseline data will be reported. 
Demographics and infant’s medical history: 
Site of enrolmentAge at enrolment (days)Sex (male/female)Place of residence (state)Number of biological siblings and birth order (integer)Infant and parental ethnicityParental country of birthParental education (highest achievement: primary school, secondary school, TAFE or trade certificate, bachelor-level university degree, post-graduate university qualification)Combined parental income (≤ $18,000, $18,001 to $37,000, $37,001 to $87,000, $87,001 to $180,000, > $180,000)Child attends daycare (yes/no, days per week)Pet ownership (dog or cat at home; kept inside, outside, or both)Breastfeeding status (exclusively, partially, or not fed with breast milk in the week before enrolment)Birth history: 
Maternal gravidity and parity (integers)Delivery type (vaginal, forceps/vacuum assisted, elective Cesarean section, emergency Cesarean section)Intrapartum antibiotics (yes/no)Neonatal systemic antibiotics (yes/no)Gestational age at delivery (weeks and days)Birth weight (grams)Length (cm)Head circumference (cm)Apgar score at 1 and 5 min (0 to 10)Hepatitis B vaccine at birth (yes/no)Maternal immunisation history confirmed where possible on Australian Immunisation Register (AIR) or through vaccination providers: 
Maternal receipt of pertussis booster vaccination in the preceding pregnancy (yes/no) and type of pertussis-containing vaccine givenMaternal receipt of pertussis booster vaccination in the preceding 5 years (not including preceding pregnancy) (yes/no)Maternal seasonal influenza vaccination during preceding pregnancy (yes/no)Family history of atopic diseases: 
At least one first degree relatives with any clinician diagnosed atopic disease (asthma, allergic rhinitis, atopic dermatitis, IgE-mediated food allergy, no family history of atopy)Physical examination at enrolment: 
Temperature (Celsius scale)Weight (grammes)Length (cm)Head circumference (cm)

### Analysis sets

The planned analysis populations are defined as in Table 1.

**Table 1 Tab1:** Pre-defined analysis sets to be used in summaries and analyses

Population	Description
Intention-to-treat (ITT)	All randomised participants with their treatment group as randomised. Participants who received vaccines/medications violating the exclusion criteria but were enrolled will be included.
Per-protocol (PP)	All randomised participants who received as planned the vaccine strategy to which they were randomised, and who completed the whole study period according to the protocol (satisfied inclusion and exclusion criteria, and visits as scheduled).
Stage 1 assays (ITT)	All participants in the ITT set who were enrolled under stage 1 protocol at the Perth Children’s Hospital (PCH)/Telethon Kids Institute (TKI).
Stage 1 assays (PP)	All participants in the per-protocol set who were enrolled under stage 1 protocol at PCH/TKI site and who met none of the stage 1 per-protocol exclusion criteria and who did not receive any contraindicated vaccines or medications for stage 1.
Stage 1+2 assays (ITT)	All participants in the ITT who were enrolled under stage 1 protocol or under the stage 2 protocol at PCH/TKI who consented for the blood samples.
Stage 1+2 assays (PP)	All participants in the stage 1 assay set with the inclusion of the additional participants enrolled under the stage 2 protocol at PCH/TKI who consented for the blood samples and who satisfied all stage 1 and 2 inclusion/exclusion criteria.

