### Exclusion criteria

The participant may not enter the trial if any of the following apply: 
History of pre-existing parent-reported clinician diagnosed IgE-mediated food allergy.History of parent-reported, clinician-diagnosed pertussis infection.Receipt of any prior vaccine, except for a single birth dose of hepatitis B vaccine within the first 7 days of life (only for visit 1).Contraindication to any routine infant immunisation: history of allergy, including anaphylaxis, to any vaccine or vaccine component.Contraindication to paracetamol.Receipt of investigational vaccines/drugs, other than the vaccines used in the study, since birth or their planned use during the study period, until the final study visit (i.e. at approximately 19 months of age).Receipt, or planned receipt, of any non-routine vaccines within 14 days after the first dose of pertussis containing vaccine.Receipt of more than 2 weeks of immunosuppressants or immune modifying drugs (e.g. prednisolone >0.5 mg/kg/day).Serious chronic illness including severe congenital anomalies affecting heart, brain, and/or lungs.History of any neurologic disorders or seizures.Administration of immunoglobulins and/or any blood products since birth or planned administration during the study period.Planned travel to any region that remains at risk of a poliomyelitis transmission at any time before study visit 8 for stage 1, and for stage 2, before the final phone/electronic contact at approximately 19 months of age.Parents or LAR who plan to move out of the geographical area where the study would be conducted.Any other significant disease or disorder which, in the opinion of the investigator, either may put the participants at risk because of participation in the trial, or may influence the result of the trial, or the participant’s ability to participate in the trial.

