### Exclusion from per-protocol population

The following criteria will be checked at each visit subsequent to the first visit. If any become applicable during the study, it will not require automatic withdrawal of the participants from the study, but may determine the participant’s evaluability in the per-protocol (PP) analysis. The data would, however, continue to be included in the intention-to-treat (ITT) analysis. 
Use, or planned use, of any investigational or non-registered product (drug or vaccine) other than the study vaccine(s) during the study period, until 1 month after the final study visit (i.e. at approximately 20 months of age).For stage 1 only: Chronic administration (defined as more than 14 days) of immunosuppressants or other immune-modifying drugs during the study period (for corticosteroids, this will mean prednisone ≥0.5 mg/kg/day, or equivalent. Inhaled and topical steroids are allowed).For stage 1 only: 
Administration of a vaccine not foreseen by the study protocol within 14 days after any scheduled vaccine dose.Administration of immunoglobulins and/or any blood products during the study period.Administration of any of the vaccines used in the study outside of the stipulated period.Administration of any live vaccines, those containing tetanus- or diphtheria-related antigens or those that contain bacterial lipo-polysaccharide or other adjuvanted vaccines between study visit 3 and study visit 5.

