## Objectives and outcomes

### Primary

The primary objective is to determine whether, compared to the standard strategy of 3 priming doses of aP (aP-only), a mixed wP/aP schedule (first dose of wP followed by doses of aP) protects against the development of IgE-mediated food allergy.

The primary outcome is history of IgE-mediated food allergy at the age of 12 months and confirmed, where necessary, by oral food challenge (OFC) before 18 months. A participant will be considered to have the outcome if there is evidence of sensitisation to a food on skin prick test (SPT), and either: 
Unequivocal IgE-mediated food allergy, defined as (i) a positive oral food challenge, or (ii) history of clinician-diagnosed food anaphylaxis, with symptoms affecting at least 2 of the following: skin, gastrointestinal tract, respiratory tract, and cardiovascular system,Highly probable IgE-mediated food allergy, defined as history of food allergic reaction consistent with PRACTALL criteria [3].

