### Analysis of primary outcome

Descriptive counts and proportions of the primary outcome will be tabulated by treatment group, including the number of inconclusive results.

Inferences for the primary outcome will be based on Bayesian models. Each model will be inferred separately for the ITT and PP analysis sets. Interest lies in the measure of effect of assignment to the study vaccine on the primary endpoint relative to the comparator vaccine, denoted by *δ*. Depending on the model, this might represent the difference in proportions meeting the primary outcome, or some transformation of these proportions (log odds-ratio). In either case, the primary statistical hypotheses are: 
$$\mathrm{H}_{0}:\delta\geq 0\ \text{vs.} \mathrm{H}_{1}:\delta <0 $$

At the final analysis, evidence of effect will be quantified as the posterior probability that *δ*<0 (that is, assignment to the study vaccine reduces the risk of IgE-mediated food allergy), conditional on the specified model given the data observed. If this posterior probability meets a pre-specified threshold of evidence, *q*, then a decision of superiority is recommended at the final analysis (trial success). The decision rule is (conditional on data *D*): 
$$d(D) = \left\{\begin{array}{ll} \text{success} & \text{if}\ \mathbb{P}(\delta<0|D)>q \\ \text{failure}\ & \text{otherwise}. \end{array}\right. $$

For this study, the threshold for assessing superiority is *q*=0.95. This value was chosen based on simulation studies investigating the effect of the interim analysis stopping rules on the probability of false positives, false negatives, and expected sample size.

Although a conclusion of superiority is recommended by the formal test of the above hypotheses, effect sizes will be presented as summaries (mean, median, and 95% credible interval (CrI)) of the posterior density obtained at the final analysis in addition to the posterior probability of superiority.

The primary analysis of the outcome will use independent Beta-Binomial models for the response proportion in the two study arms. In this case, *δ*=*θ*_*w*_−*θ*_*a*_, the difference in probability of IgE-mediated food allergy between the two vaccine strategies. In this analysis, data will be pooled across sites. Beta(1,1) priors will be assumed for both response probabilities.

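### One per-protocol definition, running to about 19 months, is applied to outcomes fixed at 6 and 12 months, so already ascertained outcomes leave the per-protocol analysis because of later events

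*SAP article*

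**What the plan says.** - **PP set (Analysis sets, Table 1).** There is one general PP row. Infants must have received the strategy to which they were randomised and be among those "who completed the whole study period according to the protocol (satisfied inclusion and exclusion criteria, and visits as scheduled".
- **End of study (Exclusion criteria).** The period for other investigational products runs "until the final study visit (i.e. at approximately 19 months of age"; the stage 2 travel criterion refers to the period "before the final phone/electronic contact at approximately 19 months of age". Under Blinding, every infant is due a vaccine at 18 months.
- **Further PP criteria (Exclusion from per-protocol population).** The investigational-product criterion runs "until 1 month after the final study visit (i.e. at approximately 20 months of age". The criteria in that section do not force withdrawal, "but may determine the participant’s evaluability in the per-protocol (PP) analysis", and the data stay in the ITT analysis.
- **Primary outcome (Objectives and outcomes, Primary).** It is "history of IgE-mediated food allergy at the age of 12 months and confirmed, where necessary, by oral food challenge (OFC) before 18 months". The atopic dermatitis and skin prick outcomes are set at 6 or 12 months.
- **Use of the set.** For the primary outcome, "Each model will be inferred separately for the ITT and PP analysis sets". Analysis of secondary outcomes applies both sets to the clinical and mechanistic outcomes.
- **Stage 1+2 assays (PP), Table 1.** This row is built from "All participants in the stage 1 assay set with the inclusion of the additional participants" enrolled under stage 2 at PCH/TKI.

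**The concern.** A per-protocol analysis of a 12-month outcome should depend on what happened up to the time the outcome was established. Here membership depends on events up to about 19 months. An infant who received the allocated vaccines, was assessed at 12 months and has a settled outcome is removed if a later visit or the last contact does not go to plan. Nothing about that infant's exposure or outcome is in doubt.

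Two things are at stake, both confined to the PP analysis. Valid outcomes are discarded, which widens its posterior. Selection also takes place after the outcome is known: families aware of a food allergy may stay or leave at different rates from others, and if that pattern differs by arm, the PP estimate of δ shifts. A reader who compares the ITT and PP results could then attribute to adherence a difference that comes from late follow-up.

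**Working it through.** **1. Timeline.** Primary outcome: 12 months, or before 18 months where OFC is needed. End of study: about 19 months. For an infant settled at 12 months the gap is 19 − 12 = 7 months. On the simulation assumption (Scenarios: outcome 48 to 72 weeks after randomisation, mean 60) and entry at 6 to <12 weeks (midpoint 9), mean age at outcome is 9 + 60 = 69 weeks, about 16 months, and the mean gap is about 3 months. Either way, membership is decided after the outcome.

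**2. The plan's own figure.** Table 3 gives, for 10% versus 7%, power 0.85 and expected sample size 2251, and type I error 0.05. A simulation of the stated design (3000 replicates, Beta(1,1) priors, normal approximation to the posterior probability, interim analyses every 200 outcomes, 16 per week) gave power 0.850, expected size 2266, type I error 0.052 and 10 interim analyses. Futility stopping under the null came out somewhat higher than in Table 3 (0.74 against 0.69); nothing below rests on it. The stated power is reproduced and is not in dispute.

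**3. Precision lost in PP.** The document gives no rate of loss between outcome and study end, so 5% to 20% is assumed. For a fixed design with n per arm and one-sided 0.05,

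power = Φ[(0.03 − 1.645·s0)/s1], where s0 = √(2 × 0.085 × 0.915/n) and s1 = √((0.10 × 0.90 + 0.07 × 0.93)/n).

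At n = 1500: s0 = 0.01018, s1 = 0.01017, power 0.904. This exceeds 0.85 because it has no early stopping; it serves only as the reference for the rows below.

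| Late loss (assumed) | Outcomes dropped of 3000 | n per arm | PP power |
|---|---|---|---|
| 0% | 0 | 1500 | 0.904 |
| 5% | 150 | 1425 | 0.890 |
| 10% | 300 | 1350 | 0.875 |
| 15% | 450 | 1275 | 0.858 |
| 20% | 600 | 1200 | 0.839 |

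**4. Bias in PP.** With true risk p, and retention r1 in allergic and r0 in other infants, the PP proportion is p·r1/(p·r1 + (1 − p)·r0). All retention rates are assumed.

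- *Loss unrelated to outcome and arm (10% throughout).* 10% versus 7% stays at 10% versus 7%; δ = −0.030.
- *Loss related to outcome, same in both arms (r1 = 0.95, r0 = 0.88).* For p = 0.10: 0.095/(0.095 + 0.792) = 0.107. For p = 0.07: 0.0665/(0.0665 + 0.8184) = 0.075. δ = −0.032 instead of −0.030, and the odds ratio is unchanged at 0.677. Under the null both arms read 10.7% and δ = 0.
- *Loss related to outcome, differently by arm (control r1 = 0.95, r0 = 0.90; wP r1 = 0.85, r0 = 0.90).* Null: control 0.095/0.905 = 0.105, wP 0.085/0.895 = 0.095, so δ = −0.010. True −0.030: wP 0.0595/0.8965 = 0.066, so δ = −0.039.

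Only in the last case does the PP analysis show an effect where there is none.

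**The case against.** The strongest reply is that little depends on this set. ITT contains every randomised infant, so no outcome is lost to the trial. That stands, and it limits the point to the PP analysis.

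A reader might infer that the PP result is biased as planned. The documents do not support this. Loss that depends on outcome alone leaves δ at 0 under the null and the odds ratio unchanged. A false effect needs the dependence to differ by arm, and parents and follow-up staff are blinded until study completion. Blinding makes that less likely without excluding it.

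A reader might also infer that the interim analyses are compromised, because PP status is unknown for infants still in follow-up. The stopping rules count participants who have reached the primary endpoint, those enrolled and those still to be enrolled; they apply no PP filter.

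Nor is it right to say that the plan leaves the deciding set wholly open. Analysis of primary outcome defines δ as an effect of assignment, which points to ITT, although the set is never named as decisive.

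Product use up to 20 months is not an automatic exclusion, since the wording there is discretionary. The completion clause in Table 1 carries no such qualifier.

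Finally, the Stage 1+2 assays (PP) row does not show that the non-inferiority claim for pertussis toxin rests on infants who are not per-protocol. The vaccine response section does not say whether that claim uses the ITT or the PP assay set, and in a PP row the starting set most naturally means Stage 1 assays (PP). This is loose wording.

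A single whole-study PP set is a possible choice, and visit windows may well be in the protocol. But the article does state the membership rule, and as stated it does not fit a 12-month outcome.

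**Conclusion.** The point holds for the PP analyses of the primary outcome and of the 6- and 12-month clinical secondary outcomes. The stated rule removes ascertained outcomes because of later events. Wherever there is late loss, precision is lost: 150 to 600 of at most 3000 outcomes, and fixed-sample PP power of 0.890 to 0.839 against 0.904, for an assumed loss of 5% to 20%. Bias is a possibility, not a demonstrated fact; in the arm-dependent illustration it amounts to about one percentage point in δ, on assumed retention rates. The ITT analysis and the published operating characteristics stand as they are. The change is worth making before the final analysis because it is specific and nearly free.

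**What to change.** Define PP per outcome in Table 1:

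- **Primary and 6/12-month outcomes:** eligible, received the randomised strategy for the doses due before the outcome, with compliance and listed violations assessed only up to ascertainment of that outcome (the 12-month assessment, or OFC where needed).
- **18/19-month serology:** compliance up to the relevant blood draw.

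Two minor clarifications can go in at the same time. State that the ITT set drives the decision rule d(D) and the interim rules. Word the Stage 1+2 assays (PP) row as Stage 1 assays (PP) plus stage 2 PCH/TKI infants in the PP set who consented to blood samples.

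The cost is SAP wording and the code that derives the sets. No new data are needed, and the simulations do not have to be rerun.

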### Analysis of primary outcome

Descriptive counts and proportions of the primary outcome will be tabulated by treatment group, including the number of inconclusive results.

Inferences for the primary outcome will be based on Bayesian models. Each model will be inferred separately for the ITT and PP analysis sets. Interest lies in the measure of effect of assignment to the study vaccine on the primary endpoint relative to the comparator vaccine, denoted by *δ*. Depending on the model, this might represent the difference in proportions meeting the primary outcome, or some transformation of these proportions (log odds-ratio). In either case, the primary statistical hypotheses are: 
$$\mathrm{H}_{0}:\delta\geq 0\ \text{vs.} \mathrm{H}_{1}:\delta <0 $$

At the final analysis, evidence of effect will be quantified as the posterior probability that *δ*<0 (that is, assignment to the study vaccine reduces the risk of IgE-mediated food allergy), conditional on the specified model given the data observed. If this posterior probability meets a pre-specified threshold of evidence, *q*, then a decision of superiority is recommended at the final analysis (trial success). The decision rule is (conditional on data *D*): 
$$d(D) = \left\{\begin{array}{ll} \text{success} & \text{if}\ \mathbb{P}(\delta<0|D)>q \\ \text{failure}\ & \text{otherwise}. \end{array}\right. $$

For this study, the threshold for assessing superiority is *q*=0.95. This value was chosen based on simulation studies investigating the effect of the interim analysis stopping rules on the probability of false positives, false negatives, and expected sample size.

Although a conclusion of superiority is recommended by the formal test of the above hypotheses, effect sizes will be presented as summaries (mean, median, and 95% credible interval (CrI)) of the posterior density obtained at the final analysis in addition to the posterior probability of superiority.

The primary analysis of the outcome will use independent Beta-Binomial models for the response proportion in the two study arms. In this case, *δ*=*θ*_*w*_−*θ*_*a*_, the difference in probability of IgE-mediated food allergy between the two vaccine strategies. In this analysis, data will be pooled across sites. Beta(1,1) priors will be assumed for both response probabilities.

### Adjusted analysis

A secondary supportive analysis of the primary outcome will use logistic regression to estimate a covariate adjusted odds ratio associated with the study vaccine strategy. The prognostic baseline covariates to be included as fixed effects are: 
SexStudy siteBreastfeeding status (exclusively, partially, or not fed with breast milk in the week before enrolment)Birth order (first born versus subsequent birth order)Combined parental income (≤ $18,000, $18,001 to $37,000, $37,001 to $87,000, $87,001 to $180,000, > $180,000)Mode of delivery (Cesarean section versus not Cesarean section)Family history of atopic disease (first degree relative with food allergy versus not)

We will specify weakly informative Student *t*priors for regression coefficients with 4 degrees of freedom, 0 mean, and standard deviation of 1.75. Inference will be based on Markov chain Monte Carlo (MCMC) samples.

### Interim analyses

This trial includes interim analyses to be undertaken at pre-specified sample sizes to recommend whether the trial should be stopped early for futility or expected success.

The recommendations are made in accordance with pre-specified stopping rules based on the data available at the time of the interim. The decisions on whether to stop are informed by Bayesian predictive probabilities of treatment effect [16].

Interim analyses begin after 200 subjects have complete primary outcome data. Subsequent interim analyses will occur after every additional 200 subjects with complete primary outcome data until either a stopping rule is met or enrolment completed. Once a decision to stop has been made, or enrolment has reached the maximum sample size, enrolment will cease and all participants will be followed to study completion.

Due to the timing of the primary outcome, the number of interim analyses is conditional on enrolment rates. Under the assumed accrual rate (Table 2), approximately 10 interim analyses are expected.

**Table 2 Tab2:** Summary of trial scenarios explored

Parameter	Values considered
Accrual	Constant rate of 16 per week (required accrual)
	Constant rate of 5 per week (slow accrual)
	Ramp-up (slow initially, increasing over course of study)
Time to outcome	Uniform between 48 and 72 weeks
Control response	0.1
Treatment response	0.05, 0.06, 0.07, 0.08, 0.09, 0.10
Superiority threshold	0.95, 0.955, 0.96, 0.965, 0.97
Success threshold	1, 0.975, 0.95, 0.925, 0.9, 0.8
Futility threshold	0, 0.025, 0.05, 0.075, 0.1, 0.2

The process for interim decisions is as follows. Let $\mathbb P(\delta < 0|D_{k})$ denote the posterior probability of superiority under the specified model conditional on data, *D*_*k*_, at interim *k*=1,...,*K*. We specify a prediction model, $f(\tilde D_{k}|D_{k})$ for future outcome data $\tilde D_{k}$ that uses the data observed so far, marginalised over any uncertainty in the prediction model parameters. Using predictions of the primary outcome for subjects enrolled who are yet to complete follow-up, as well as subjects yet to be enrolled, the stopping decision is based on the predicted outcome of the trial (in terms of the decision rule used at the final analysis) if enrolment were stopped now (with follow-up completed on enrolled participants), or continued to the maximum sample size, given what has been observed up to interim *k*.

The predicted probability of success (PPoS) [17] is calculated as 
$$\text{PPoS}_{k}(q) = \mathbb E_{\tilde D_{k} | D_{k}}\left[\mathbf{1}_{(q,1]}\left\{\mathbb P(\delta<0|D_{k},\tilde D_{k})\right\}\right] $$ and is the probability that superiority would be decided at a final analysis using threshold *q* and future data $\tilde D_{k}$ according to $f(\tilde D_{k}|D_{k})$.

The value of PPoS_*k*_ depends on the specified prediction model. In this trial, the posterior predictive distribution of the primary analysis model is used as the prediction model. This is two independent Beta-Binomial distributions conditional on the observed responses in each treatment group.

